###### Organ Space

Infection occurs within 30 days after the operation if no implant is left in place or within 1 year if the implant is in place and the infection appears to be related to the operation and infection involves any part of the anatomy (eg, organs and spaces) other than the incision that was opened or manipulated during an operation and at least 1 of the following: (1) purulent drainage from a drain that is placed through a stab wound into the organ/space; (2) organisms isolated from an aseptically obtained culture of fluid or tissue in the organ/space; (3) an abscess or other evidence of infection involving the organ/space that is found on direct examination, during reoperation, or by histopathologic or radiologic examination; or (4) diagnosis of organ/space SSI made by a surgeon or attending physician.

##### Controls

Cases will be matched to controls that received the same procedure but did not develop a SSI. Further variables to be included are (1) age; (2) sex; (3) American Society of Anesthesiologists (ASA) score; (4) BMI; (5) duration of operation (as a percentile); and (6) diabetes. If available, comorbidities other than diabetes and underweight or overweight as well as the Charlson comorbidity index [15] and its components will be included.

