#### Nested Case-Control Design

The nested case-control study generates data for analyzing costs and outcomes. Participants acquiring *S. aureus* SSIs will be documented in an electronic database and matched 1:1 to controls within each center. Criteria for matching are similar epidemiological data and procedure type, but without SSI and are specified in the Data Collection section.

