### Study Procedure

#### Populations

Data will be assessed in the cohort and the nested case-control population (Textbox 1).

The following are the matching criteria for the nested case-control population: (1) type of procedure, (2) age, (3) BMI, (4) duration of procedure (as a percentile for this procedure), (5) diabetes, and (6) sex.

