#### Sample Size

We assume a 1.5% incidence rate of *S. aureus* SSI. Incidence rates can be determined with a 95% CI of plus or minus 0.5% by observing 1500 surgical procedures, assuming a mean *S. aureus* SSI rate of 1%. Lower incidence rates would result in smaller 95% CIs with a similar sample size or similar CIs with a smaller sample size. Therefore, at least 15 centers should be included in the analysis, resulting in 90,000 to 150,000 patients observed patients. This will allow us to calculate incidence rates with meaningful precision for all surgical procedures performed on at least 1% to 1.5% of respective patients. To further broaden the scope of this study, 1 or 2 centers per country will be included specializing in types of surgery not traditionally performed at academic surgical centers but highly relevant to the prevention of SSI in otherwise healthy patients (eg, plastic surgery). Assuming a 1.5% incidence rate of *S. aureus* SSI, in a population of 150,000, 2250 cases will be matched to 2250 controls.

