### Statistical Analysis

Assuming a mean *S. aureus* SSI rate of 1% [5], incidence rates can be determined with a 95% CI of plus or minus 0.5% by observing 1500 surgical procedures. Therefore, at least 15 centers will be included in the analysis, resulting in 90,000 to 150,000 observed patients. Assuming an incidence rate of *S. aureus* SSI of 1.5% in a population of 150,000, 2250 cases will be matched to 2250 controls.

Data will first be analyzed for missing values. We will perform a qualified evaluation of missingness mechanisms for each variable with more than 1% missing values. In case data are missing completely at random, patients with the missing value will be excluded from that respective analysis step (complete record analysis). For values not missing at random, multiple imputation using chained equations will be performed and compared to a complete record analysis for improved robustness of results. We will perform in-depth descriptive statistics of all parameters observed. Country-based and institution-based incidence rates will be determined for each procedure (eg, ventral hernia repair) and each category (eg, vascular surgery). For each incidence rate, the 95% CIs for a binominal proportion will be calculated. Costs will be calculated for both procedures and categories. Accounting for the usually non-normal distribution of costs in medical settings, statistical analyses (eg, CI construction) will be carried out using non-parametric bootstrap procedures. Reported SSI rates and cost will be further stratified by depth of SSI (eg, superficial, deep). Association between major cost drivers and SSI occurrence, as well as overall costs and SSI occurrence, will be determined using bootstrapped t tests.

Multivariable regression analysis will be used to confirm significance of SSI occurrence for overall treatment costs.

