#### Secondary Analysis

The secondary analysis will consist of determining the overall and procedure-specific outcomes of *S. aureus* surgical site infections in Europe as well as the overall and procedure-specific economic burden of *S. aureus* SSI in Europe. Therefore, patients having established *S. aureus* SSI will be matched 1:1 to controls from the same center based on a propensity score and optimal matching with the following covariates: (1) type of procedure, (2) age, (3) ASA score, (4) BMI, (5) duration of procedure (as percentile for this procedure), (6) diabetes, and (7) sex.

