With SSI rates being the primary endpoint, SSI detection methodology is crucial in this study. Prior studies and surveillance effort, if specifying detection methodology at all, are usually limited to the analysis of administrative code data [14,15]. However, a recent publication demonstrated that using bacteriological data is superior and combining both—administrative and bacteriological data—could be even more advantageous [16]. In this very study, the detection by means of bacteriologic data will result in high sensitivity, specificity, and negative predictive values (96.4%, 91.4%, and 99.9%, respectively) for deep SSI with no significant difference to the use of both types of data.

Cases are matched 1:1 to controls within each center by software provided by the coordinating center. Matching cases and controls within centers addresses the need for risk-adjustment to institutional characteristics and practices. Cases are matched to controls that received the same type of procedure. Individual pair-wise matching will be used, utilizing optimal matching to ensure the overall smallest possible Euclidean distance between cases and controls. Acknowledging the limited utility of using the National Healthcare Safety Network (NHSN) risk index, which only accounts for the existence of certain risk factors but not their composition, a propensity score is determined by logistic regression.

Costs are calculated by multiplication of the per-unit price for major cost drivers with the number of units used. Minor cost drivers, such as drug use, will be disregarded, as length of stay has been repeatedly shown to account for 90% of excess SSI costs [11].

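### Controls need not still be at risk when the case's infection is diagnosed, so excess index stay and cost are overstated and mortality counted from surgery is understated

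*Protocol article*

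**What the plan says.** The protocol article defines controls by their eventual infection status. Nested Case-Control Design asks for patients with "similar epidemiological data and procedure type, but without SSI", and Controls repeats it: "Cases will be matched to controls that received the same procedure but did not develop a SSI".

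The matching variables are listed in three places:
- Populations gives "1) type of procedure, (2) age, (3) BMI, (4) duration of procedure (as a percentile for this procedure), (5) diabetes, and (6) sex".
- Controls adds ASA score and, if available, further comorbidity.
- Secondary Analysis matches within center "based on a propensity score and optimal matching with the following covariates", again all baseline or operative. Duration here means duration of the operation.

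The outcomes are whole quantities: length of hospitalization, ICU stay, and survival at 30 and 90 days (Textbox 1). The cost calculation in Exploratory Analysis uses whole stay, ICU stay, ventilation hours and revision surgeries. Statistical Analysis compares them by infection status: "Association between major cost drivers and SSI occurrence, as well as overall costs and SSI occurrence, will be determined using bootstrapped t tests", followed by multivariable regression of cost. Principal Findings states that "length of stay has been repeatedly shown to account for 90% of excess SSI costs".

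The date of SSI diagnosis is collected in the cohort (Data Collection, Cohort), but no section uses it in matching or analysis. Neither Limitations section mentions the timing of infection.

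**The concern.** For the secondary objectives SSI is the exposure, and the Rationale wants controls that allow the extra cost caused by SSI to be isolated. SSI is acquired at some point after surgery. A patient infected during the index stay must have stayed long enough for that to happen, and every case must have lived to be diagnosed. A never-infected control meets neither condition. Close matching on baseline variables cannot remove a difference that arises from time after surgery.

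Two distortions follow, in opposite directions. Index stay and its cost look too high in cases. Mortality counted from surgery looks too low in cases. The first falls on the component that the article itself treats as dominant in excess cost. All secondary objectives on outcome and economic burden draw on this comparison, as does the exploratory estimate of economic burden.

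**Working it through.** **The plan's own figure.** 150,000 × 0.015 = 2250, which reproduces "2250 cases will be matched to 2250 controls". The article gives no effect size, SD or stay distribution for the cost and survival comparison. Everything below therefore rests on stated assumptions and assumes that SSI has no effect.

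**1. Index stay, onset in hospital only.** Let stay L have mean m and coefficient of variation CV. With a constant infection hazard in hospital, the chance of becoming a case is proportional to L, so cases have mean stay m(1 + CV²) and the false excess is m·CV². With m = 8 days:
- CV 0.5: 8 × 0.25 = 2.0 days
- CV 0.7: 8 × 0.49 = 3.9 days
- CV 1.0: 8 × 1.00 = 8.0 days

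**2. Allowing for readmission.** Let onset be uniform over 30 days, and let a fraction q of post-discharge onsets be captured at readmission. The chance of becoming a case is then proportional to min(L, 30) + q·(30 − min(L, 30)). Ignoring the few stays beyond 30 days, the false excess in index stay is

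(1 − q)·m²·CV² / [(1 − q)·m + 30q].

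At q = 0.25 and CV 0.5 this is 0.75 × 64 × 0.25 / (0.75 × 8 + 7.5) = 12 / 13.5 = 0.89 days. With gamma stays and the 30-day cap kept:

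| q | CV 0.5 | CV 0.7 | CV 1.0 |
|---|---|---|---|
| 0 | 2.0 | 3.9 | 7.3 |
| 0.25 | 0.9 | 1.7 | 3.2 |
| 0.5 | 0.4 | 0.8 | 1.5 |
| 1 | 0 | 0 | 0 |

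The cap explains 7.3 here against 8.0 in step 1.

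**3. Other stay and onset patterns, in-hospital onset only (q = 0).** A simulation used mean stay 5, 8 or 12 days, gamma shape 1 or 2, and median potential onset at day 5 or 10. Never-infected controls gave a false excess of 2.6 to 9.0 days. Controls still in hospital, alive and uninfected on the case's onset day, with stay counted from that day, gave −0.14 to +0.17 days, which is simulation noise.

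**4. Mortality counted from surgery.** With a constant death hazard and mean onset at day 7.9, a case is exposed to 30-day death for only 30 − 7.9 = 22.1 days.
- Assumed 30-day mortality 5%: 1 − 0.95^(22.1/30) = 3.7% in cases. The simulation gave 3.5% against 5.0% in controls.
- Assumed 30-day mortality 2%: 1 − 0.98^(22.1/30) = 1.5%. Across the simulated patterns it was 1.4% to 1.7% against 2.0%.

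At-risk controls agreed with cases within simulation noise.

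**The case against.** The strongest objection concerns size. Detection links all positive cultures to surgical patients, and readmissions with their attribution to SSI are recorded. A patient diagnosed at readmission did not have to remain in hospital to become a case, so the stay bias arises only to the extent that post-discharge infections are missed. This stands. A reader might infer a false excess of 2 to 12 days (12 being the value at CV 1.0 if infection can start only from day 4). That range sets q to 0, and the documents give no q. The Limitations section in the Discussion says that late infections after discharge will be missed, which argues against q near 1 but does not fix a value.

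Three further readings are tempting but unsupported:
- A reader might infer that implant cases diagnosed after day 90 have 100% survival at 90 days by construction. That holds only if time runs from surgery and such cases are included. No time origin is stated, and the cohort list collects SSI within 90 days while the deep and organ-space definitions allow 1 year with an implant.
- A reader might infer that the tests ignore pairs and centers. The article is only silent on this, and that detail can be left to the analysis plan.
- A reader might infer that attribution to SSI is recorded for everything except the index stay. Textbox 3 points that way, but the layout of Textbox 1 as extracted is ambiguous, so the point does not rest on it.

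It can also be said that Figure 1, on matching, is not shown and that an analysis plan may repair the comparison. The printed rules are nevertheless consistent with one another. Choosing controls is sampling: stay and survival are documented only for cases and their chosen controls, and the listed cohort export contains no discharge or death day. A later analysis plan could not recover controls who were still at risk.

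**Conclusion.** The concern holds in this form. As written, the plan compares cases with never-infected controls who need not have been at risk when the case was diagnosed. For infections that begin during the index stay, excess stay and cost are overstated even with no effect of SSI. For all cases, SSI-related mortality counted from surgery is understated; counted from diagnosis, it has no matching origin in controls.

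The direction follows from the control rule; the size does not come from the documents. Under the assumptions in the working (mean stay 8 days, CV 0.5 to 1.0, roughly constant infection hazard), the false excess index stay is about 2 to 8 days if no post-discharge infection is captured, about 0.9 to 3.2 days if a quarter are, and near 0 if all are. The survival problem remains even with full capture. The overall and procedure-specific incidence estimates, which are the primary objectives, do not use the matched controls and are unaffected.

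**What to change.** Make the change before controls are documented:
1. Add discharge day and death day, as days from surgery, to the cohort export.
2. Require each control to be alive, SSI-free and, where the case's infection began in hospital, still in hospital on the case's post-operative day of diagnosis.
3. Assign that day to the control as its index day. Count stay, ICU days, ventilation, cost and survival from it in both members of the pair, and state this time origin for the 30- and 90-day survival outcomes.
4. Because diagnosis can lag onset, counting from diagnosis may drop some days that SSI caused. Add a sensitivity analysis with the index day moved a few days earlier.

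A multistate model, or one with SSI as a time-dependent exposure, is an acceptable alternative if stay and death dates are exported for the whole cohort.

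The cost is two export fields and one eligibility condition in the matching software that the coordinating center supplies; the diagnosis date is already collected. The planned 2250 pairs need not change if every case finds an eligible control. The downside is fewer eligible controls for late-onset cases: in the simulated patterns 32% to 77% of never-infected patients were still at risk on the onset day, before restriction to the same center and procedure.

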#### Data Collection

##### Cohort

The following variables will be collected from EHRs for descriptive purpose only: (1) age by category; (2) sex; (3) BMI; (4) comorbidities (International Statistical Classification of Diseases and Related Health Problems [ICD-10] codes); (5) diabetes; (6) type of procedure; (7) duration of procedure; (8) occurrence of SSI related to observed procedure within 90 days, including date of diagnosis; (9) wound class.

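### The three matching lists disagree on ASA score and comorbidity, and none includes wound class, so the cost and outcome contrasts may stay partly confounded

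*Protocol article*

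**What the plan says.** **What is collected.** Data Collection, Cohort lists nine variables. Item 4 is "4) comorbidities (International Statistical Classification of Diseases and Related Health Problems [ICD-10] codes" and item 9 is wound class. Textbox 1 also shows both as cohort data. The Cohort section says its variables "will be collected from EHRs for descriptive purpose only". ASA score is in Textbox 1 but not in that nine-item list.

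**What is matched on.** Three sections answer this.

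- *Secondary Analysis*: cases are matched 1:1 within center, "based on a propensity score and optimal matching with the following covariates". Type of procedure and age come first, and the list ends "3) ASA score, (4) BMI, (5) duration of procedure (as percentile for this procedure), (6) diabetes, and (7) sex".
- *Populations* (Study Procedure): six criteria. Type of procedure, age and BMI come first, followed by "4) duration of procedure (as a percentile for this procedure), (5) diabetes, and (6) sex". ASA is absent.
- *Controls*: same procedure, plus age, sex, ASA, BMI, duration percentile and diabetes. It then says of "If available, comorbidities other than diabetes and underweight or overweight as well as the Charlson comorbidity index", and of that index's components, that they will be included.

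**Other relevant text.** Rationale lets a center obtain a waiver for single data items in the cohort export; a waived item is then documented in the nested part. Statistical Analysis plans a multivariable regression to confirm that SSI matters for overall treatment cost.

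**The concern.** The nested case-control part exists to isolate the cost and outcome attributable to *S. aureus* SSI, and Rationale says this needs well-matched controls. Pre-existing illness and contamination of the operation can plausibly raise the risk of SSI and also lengthen stay, increase ICU use and raise mortality. If cases carry more of either than their matched controls, part of the difference is credited to SSI wrongly, most likely as an overstatement. This bias does not shrink with the planned number of pairs.

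The conflicting lists also leave open which score will be fitted. If Secondary Analysis governs, comorbidity beyond diabetes is out. If Controls governs, it is in at some centers and possibly not at others, so a matched control would not mean the same thing throughout the pooled estimate. Wound class is out on either reading.

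**Working it through.** **1. The plan's own figure.** The number of pairs reproduces: 0.015 × 150,000 = 2250 cases, matched to 2250 controls (Sample Size). The point does not depend on this figure. It rests on the covariate lists.

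**2. The lists side by side.**

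| Variable | Textbox 1, cohort | Cohort list | Populations | Controls | Secondary Analysis |
|---|---|---|---|---|---|
| Procedure | yes | yes | yes | yes | yes |
| Age, sex | as demographics | yes | yes | yes | yes |
| BMI | yes | yes | yes | yes | yes |
| Duration | yes | yes | yes | yes | yes |
| Diabetes | not listed separately | yes | yes | yes | yes |
| ASA score | yes | **no** | **no** | yes | yes |
| Other comorbidity / Charlson | ICD codes | ICD-10 codes | **no** | **if available** | **no** |
| Wound class | yes | yes | **no** | **no** | **no** |

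Two rows differ between the three matching lists: ASA and comorbidity. One row, wound class, is collected for everyone and used in none of them.

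**3. The descriptive-only label.** Of the nine variables in the Cohort list, six (age, sex, BMI, diabetes, procedure, duration) are also Secondary Analysis covariates. The label is therefore wrong for most of its own list. For the same reason it cannot be read as barring comorbidity in particular. The seventh covariate, ASA, is missing from that list altogether.

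**4. Possible size.** The documents give no prevalence, imbalance or effect, so all inputs below are assumptions.

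- *Stay.* Spurious excess = post-match imbalance × days added by the comorbidity. With imbalances of 5 to 20 percentage points and effects of 2 to 6 days, the range runs from 0.05 × 2 = 0.1 day to 0.20 × 6 = 1.2 days. With 5 to 15 points and 5 to 10 days, it runs from 0.05 × 5 = 0.25 day to 0.15 × 10 = 1.5 days.
- *Mortality.* If SSI has no true effect, the spurious risk ratio is (1 + p₁(RR − 1)) / (1 + p₀(RR − 1)), where p₁ and p₀ are the prevalences in cases and controls. With p₀ = 0.30:
  - p₁ = 0.35, RR = 1.5: 1.175 / 1.15 = 1.02
  - p₁ = 0.50, RR = 3: 2.0 / 1.6 = 1.25

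These figures show how the bias scales. They do not estimate it for this study.

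**The case against.** A reader might infer that comorbidity is simply left out and that the results will therefore be confounded. The document does not support that reading, for four reasons.

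- **Comorbidity is conditionally in.** The Controls sentence says other comorbidities and Charlson will be included where available. Nested Case-Control Design also sends the reader to the Data Collection section, where Controls stands, for the matching criteria. For comorbidity the defect is therefore an inconsistency, not a plain omission. This stands.
- **Underlying illness is partly covered.** ASA, age, BMI and diabetes are in the Secondary Analysis score, and matching is within center. Residual imbalance is possible but not shown. This stands.
- **Wound class is a different matter.** It describes contamination of the operation rather than the patient's health, and matching on the same procedure absorbs part of it. This stands in part: contamination can still differ within one procedure type.
- **Cost gets a further regression.** Its covariates are not named, which an article may leave to an analysis plan. But it is described only for overall treatment cost, so it does not protect the stay or mortality comparisons.

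Nor is the availability condition needless. A center with a waiver has no value for that item in its cohort export and cannot use it to select controls. Finally, ICD-10 codes may be fuller in long, infected admissions, so adjusting for them without a timing rule could introduce bias of its own. The fix has to deal with both.

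**Conclusion.** The point holds as one of consistency with a risk of residual confounding. The three matching lists conflict on ASA and comorbidity, wound class is collected cohort-wide but is in none, and the Secondary Analysis list taken literally omits baseline risk factors already at hand. Excess cost, stay and mortality may therefore stay partly confounded. Whether they do, and by how much, cannot be determined from the document: the ranges of 0.1 to 1.5 days and of 1.02 to 1.25 for the mortality ratio rest entirely on assumed imbalances and effects. The secondary objectives are affected. The primary incidence estimates do not use the matching and are untouched. The change should be made before controls are selected, because the match cannot easily be altered afterward.

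**What to change.** 1. Put one covariate list in Populations, Controls and Secondary Analysis: the present seven, including ASA, plus wound class and a Charlson index built from the exported ICD-10 codes.
2. Restrict the Charlson index to conditions present before the index surgery, so that diagnoses coded because of the infection or the longer stay do not enter.
3. In Data Collection, Cohort, replace the descriptive-only wording with the actual uses (description and matching), and add ASA to the list.
4. Where a center has a waiver for an item, leave it out of that center's match. Adjust for it in the outcome regression from the nested-part data, for stay and mortality as well as cost.
5. Report standardized differences after matching for every covariate, including wound class and Charlson.

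The cost is small: two more model terms, no new cohort variables, and some work to apply the timing rule. The remaining downside is uneven coding depth. Within-center matching largely absorbs differences between centers, but not differences between cases and controls within a center; the pre-surgery restriction limits those without removing them.
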